## Abstract

**Background:**

Tinnitus is a highly prevalent symptom, affecting 10–15% of the adult population. Tinnitus influenced by alterations in somatosensory afference from the neck or jaw is referred to as somatic tinnitus (ST). ST is known to respond positively to physiotherapy treatment; however, it is challenging to motivate patients to systematically perform home exercises correctly, and the necessary tinnitus counselling is often lacking.

The aim of this study is twofold, namely to investigate both the effectiveness and cost-effectiveness of a blended physiotherapy program for ST, including a smartphone application designed to increase exercise therapy compliance and provide tinnitus counselling.

**Methods:**

This study is designed as a single-blind two-arm 1:1 randomised controlled trial (RCT). Adult patients diagnosed with ST, without psychiatric comorbidities and with experience in using a smartphone, will be recruited at the Ear Nose Throat (ENT) department of the Antwerp University Hospital (UZA). Patients will be randomised into two groups. The experimental group will receive the blended physiotherapy program comprising six in-clinic physiotherapy sessions over a period of 12 weeks (1x/2 weeks) and an exercise and counselling program provided by the smartphone application. The control group will receive the standard care program comprising twelve weekly in-clinic physiotherapy sessions. Each physiotherapy session has a duration of 30 min. The primary outcome measure is the change in Tinnitus Functional Index (TFI) score. Additionally, a cost-effectiveness analysis will be performed from a societal perspective considering both direct and indirect costs. There will be follow-up assessments at one and 3 months after the final treatment session.

**Discussion:**

Our study is the first to combine both tinnitus counselling and neck/jaw treatment provided by a digital application in a blended physiotherapy program. This, in order to empower ST patients to improve and better manage their own health and, possibly, reduce economic costs by alleviating the tinnitus burden that ST patients experience. The strengths of the planned RCT are the high-quality methodological design, the large sample size and the expertise of the involved multidisciplinary research team.

**Trial registration:**

Clinicaltrials.gov NCT05245318. Registered on 26 January 2022.

**Supplementary Information:**

The online version contains supplementary material available at 10.1186/s13063-022-06378-7.

Among the many potential influencing factors of tinnitus, one group exists where the tinnitus is influenced by alterations in somatosensory afference from the cervical spine or temporomandibular area, caused by, for instance, increased muscle tension or movement restrictions. This type of tinnitus is called somatic or somatosensory tinnitus (ST) and is estimated to be present in approximately 25% of tinnitus patients [11–13]. Previous studies showed that a multimodal physiotherapy treatment directed to cervical spine and temporomandibular joint (TMJ) dysfunctions can provide tinnitus relief in ST patients [14–22]. The multimodal physiotherapy treatment comprises a combination of (home) exercises, manual mobilizations and techniques to decrease muscle tension tailored to the patient’s specific cervical spine and/or TMJ dysfunction [14–17].

While the effectiveness of this multimodal physiotherapy program has been proven, there are still opportunities for improvement. Firstly, the efficacy of the home exercises could be increased, as two thirds of patients are not compliant in performing daily home exercises, and others experience difficulties to perform the exercises correctly without the guidance of a physiotherapist [23]. Secondly, the associated symptoms and comorbidities of tinnitus often demand a more multidisciplinary approach [4–7]. Apart from the physiotherapy program, patients would also benefit from additional psychological counselling and advice to account for the mental burden that comes with tinnitus [12]. Due to a lack of knowledge about tinnitus, physiotherapists often do not provide the additional tinnitus counselling, or patients receive inaccurate advice that may counteract the positive effects of the multimodal treatment. This results in suboptimal care for ST patients and often recurrent complaints that require regular treatment series in the long term. As such, ST patients would benefit from additional support to increase exercise compliance on the one hand and from the addition of psychological counselling on the other hand [4–7, 12, 23].

One way to provide these extra elements is through a smartphone application. In the last decade, computer and smartphone applications increasingly found their way into medicine and physiotherapy treatment. Recently, the COVID-19 pandemic has shown that low-contact treatment provided from a distance through applications and videoconferencing can be used as a substitution of or addition to face-to-face clinical care for several conditions [24–26]. Telerehabilitation and internet-based psychological counselling have already proven to be as effective as standard practice in relieving pain and disability in a variety of musculoskeletal conditions [27, 28] and in reducing distress in case of tinnitus [29]. The use of a smartphone application might provide additional support to motivate the patient to perform daily exercises in order to increase exercise compliance. Furthermore, it can be used to provide psychological tinnitus counselling.

Therefore, the aim of this single-blind non-inferiority two-arm parallel group 1:1 randomised controlled trial is to investigate the effectiveness and cost-effectiveness of a blended physiotherapy program for ST, including a smartphone application designed to increase therapy compliance and provide tinnitus counselling. It is hypothesised that the blended physiotherapy program will at least be as effective as the standard physiotherapy care and that this new intervention will reduce both direct and indirect costs related to ST.

## Methodology

This protocol is reported according to the Standard Protocol Items Recommendations for Interventional Trials (SPIRIT) guidelines 2013: Explanation and Elaboration: guidance for protocols of clinical trials [30].

### Patients

Adult patients (+ 18 years old) can be included in the study in case they are diagnosed with ST, according to the diagnostic criteria for ST, listed in Table 1 [31]. The diagnosis will be made by an experienced multidisciplinary team of Ear Nose Throat (ENT) specialists, audiologists, physiotherapists and psychiatrists at the University Hospital of Antwerp (UZA) (Belgium), in order to identify and take into account all potential influencing factors of a patient’s tinnitus. Patients will only be diagnosed with ST in case the somatosensory influence on the tinnitus is one of the major influencing factors. Tinnitus patients who present themselves with one or more of the ‘Accompanying symptoms’ described in Table 1 are considered suffering from ST in case their tinnitus appeared or aggravates simultaneously with the neck or jaw symptoms. Additionally, in case the occurrence of the tinnitus is closely related to a neck or head trauma, patients are considered to suffer from ST [32].

**Table 1 Tab1:** Diagnostic criteria for somatic tinnitus (ST) listed by a group of ST experts [31]

**Tinnitus modulation**	
• By voluntary movements of head, neck, jaw or eyes	
• By somatic manoeuvres	
• By pressure on myofascial trigger points	
**Tinnitus characteristics**	
• Simultaneous appearance of tinnitus and neck or jaw pain	
• Simultaneous aggravation of tinnitus and neck or jaw pain	
• Preceded neck or head trauma	
• Increasement tinnitus during certain postures	
• Varying tinnitus pitch, loudness and/or location	
• For unilateral tinnitus, the audiogram does not account for unilateral tinnitus	
**Accompanying symptoms**	
• Frequent pain in the cervical spine, head or shoulder girdle	
• Presence of pressure tender myofascial trigger points	
• Increased muscle tension in the suboccipital muscles	
• Increased muscle tension in the extensor muscles of the cervical spine	
• Temporomandibular disorders	
• Teeth clenching or bruxism	
• Dental disease	

Patients should be fluent in Dutch, in order to complete all questionnaires and perform all tests (including speech-in-noise tests). Additionally, all included patients should own a smartphone and should be able to use the most common applications without support. Patients with other types of tinnitus, active middle ear pathology or diagnosed psychiatric disorders will be excluded from the study.

### Study design and randomisation procedure

The study is designed as a single-blind two-arm 1:1 randomised controlled trial. After baseline measurements, patients will be randomised into either the experimental group or the control group. A stratified randomisation according to the grade of tinnitus severity obtained by use of the Tinnitus Functional Index (TFI) and gender will be used. The TFI categorises patients from grade 1 (no tinnitus distress) to grade 5 (very severe tinnitus distress) [33–35]. Only grades 2–5 are considered for this study: light distress (7 to 28), moderate distress (29 to 47), severe tinnitus distress (48 to 65) and very severe tinnitus distress (66 to 100) [35]. The stratified randomisation assures an even distribution of patients of each tinnitus grade and of men and women in both treatment arms. A minimisation procedure will be used to perform the stratified randomisation using the web-based online randomisation tool Qminim [36]. Patients will be informed that the study investigates the effectiveness of two different physiotherapy approaches for ST but will not receive in-detail information about the content of the treatment before randomisation. Hence, patients are blinded towards the group they are randomised to. The therapist cannot be blinded. To limit the risk of bias related to lack of blinding of the therapist, all evaluation measurements will be performed by a blinded assessor and data analysts will be blinded as well. An overview of the study design and randomisation procedure is presented in Fig. 1.

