#### Primary outcome measure

The primary outcome is the change in Tinnitus Functional Index (TFI) score from baseline to 1 month after the treatment. This time point was chosen since previous research indicated that the largest treatment effect on TFI is to be expected 1 month after the last treatment session [37–40]. For the cost-effectiveness analysis, an additional time point, immediately after the last treatment session, is added to be able to link the amount of decrease on TFI to the EuroQoL (EQ)-5D-5L that assesses HRQOL. The TFI is a self-report questionnaire comprising 25 questions, each scored on an eleven-point Likert scale, objectifying the impact and severity of tinnitus. Eight subscores are differentiated, namely intrusiveness, sense of control, cognitive complaints, sleep disturbance, auditory difficulties, relaxation, quality of life (QOL) and emotional distress. The total score and subscores will be noted on a scale of 0 to 100 with higher scores indicating higher levels of tinnitus-related distress [33, 34]. A change of 13 points out of 100 is considered a clinically relevant change [33]. TFI has a high sensitivity to change, a good test-retest reliability (*r*: 0.78), discriminant validity with the Beck Depression Inventory-Primary Care (*r*: 0.56) and convergent validity with both the Tinnitus Handicap Inventory (THI) (*r*: 0.86) and the visual analogue scale (VAS) for tinnitus loudness (*r*: 0.75) [33, 41, 42].

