##### Questionnaires related to the cost-effectiveness analysis

EuroQoL (EQ)-5D [58]

The EuroQoL EQ-5D questionnaire is the most commonly used method to collect health-related Quality of Life (HRQOL) data and is recommended by worldwide economic evaluation guidelines such as the NICE recommendations [59, 60]. This questionnaire measures HRQOL using 5 dimensions: mobility, self-care, usual activities, pain/discomfort and anxiety/depression [58]. The response pattern produces a code which represents a health state of the participant. Each health state is associated with a health utility value between 0 and 1 in which 0 represents death and 1 corresponds to perfect health [60]. To calculate utility values, the recently published utility value sets for Belgium will be used [61]. HRQOL is necessary to calculate quality-adjusted life years (QALYs), the most important outcome from the health economics point of view [60]. The five level (5 L)-version is preferred over the three level (3 L)-version as it is more nuanced and thus more sensitive to gains (or losses) in general health [62]. The EQ-5D-5L will be assessed at baseline and both follow-up moments and will additionally be collected after the final treatment session.Productivity Cost Questionnaire (*i*PCQ) [63]

The iMTA Productivity Cost Questionnaire (*i*PCQ) includes three modules measuring productivity losses of paid work due to (1) absenteeism and (2) presenteeism (productivity loss due to paid work) and productivity losses related to (3) unpaid work. The *i*PCQ delivers the necessary input to calculate productivity loss. *i*PCQ will be collected monthly, meaning every 3 to 5 weeks. To organise this systematically, patients of the intervention group will be asked to complete this questionnaire at treatment session two, four and six and patients of the control group at treatment session four, eight and twelve. Both groups will additionally receive the *i*PCQ at 1 month follow-up and 3 months follow-up, as defined above. An additional two-month follow-up moment is planned for the *i*PCQ (range: 3 to 5 weeks after 1 month follow-up assessment).

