This study will use a high-quality methodological design to perform a single blind two-arm randomised controlled trial. A total of 334 patients will be randomised into two groups and the current standard care will be compared to the use of a blended physiotherapy program. In studies investigating physiotherapy treatment, blinding of subjects and therapists is typically difficult. In our study, patients will be blinded towards the group they will be randomised to, but the therapist cannot be blinded, as she knows whether a patient receives the treatment every week or every 2 weeks. To limit the risk of bias related to lack of blinding of the therapist, all evaluation measurements will be performed by a blinded assessor. All physiotherapy sessions will be provided in the clinic by the same therapist. This approach was chosen to ensure all patients will receive the same treatment and to limit therapist-dependent differences in outcome in our study. This approach might decrease the transferability of our study results to a clinical situation but was deemed necessary to avoid bias.

The proposed approach of the blended physiotherapy program using a smartphone application offering both an exercise program and tinnitus counselling has never been used before in ST treatment. Similar app-based programs, however, have proven to be effective and feasible for the treatment of neck pain [69, 70]. There is also an increasing interest in the use of smartphone applications for tinnitus patients [71, 72]. This study combines both tinnitus counselling and neck/jaw treatment providing a digital application to empower ST patients to improve and better manage their own health. Earlier research has already proven that the content of the application, both the exercise program and the counselling, is effective when used in a clinical face-to-face setting [14–22, 73, 74]. However, it was never examined in the context of a smartphone application as part of a blended physiotherapy treatment. The use of our developed smartphone application is expected to help overcome common hurdles related to the in-clinic treatment of patients with ST.

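### Patients are described as blinded, but they know which treatment they receive and they rate the self-reported primary endpoint themselves

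*Protocol article*

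**What the plan says.** Under Study design and randomisation procedure, patients are told that two physiotherapy approaches are being compared, but they "will not receive in-detail information about the content of the treatment before randomisation". The article then concludes: "Hence, patients are blinded towards the group they are randomised to". The same section offers a blinded assessor and blinded data analysts as protection against the therapist being unblinded.

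The Discussion repeats the claim: "patients will be blinded towards the group they will be randomised to, but the therapist cannot be blinded". The reason given for the therapist is "as she knows whether a patient receives the treatment every week or every 2 weeks".

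The two treatment sections describe the arms:
- **Control:** twelve weekly sessions, no support for home exercises between sessions, and no tinnitus counselling.
- **Experimental:** six sessions, one every two weeks, plus an app with a daily exercise programme and two tinnitus counselling sessions a week.

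On the primary endpoint, the article states: "The TFI is a self-report questionnaire comprising 25 questions".

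**The concern.** The conclusion about patient blinding does not follow from its premise. What a patient is told before randomisation does not settle what that patient knows during twelve weeks of treatment, or when completing the TFI one month later. The arms differ in ways that the patient experiences directly, and neither a sham app nor a matched visit schedule is described.

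This matters because the patient is the rater of the primary endpoint. The VAS for loudness, the EQ-5D-5L and the iPCQ are also patient-reported. Knowing one's own treatment can affect such ratings, and the margin is only 6.5 points on a 0–100 scale, so a modest shift can change a non-inferiority conclusion. Calling patients blinded tells the reader that this route to bias is closed when it is open.

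**Working it through.** **1. What each party knows after allocation**

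| Feature | Control | Experimental | Patient knows own? | Therapist knows? |
|---|---|---|---|---|
| Visit frequency | weekly, 12 in total | every 2 weeks, 6 in total | yes | yes, and this is the stated reason she is unblinded |
| App with daily exercises | no | yes | yes | not stated as a reason |
| Tinnitus counselling | none | by app, twice a week | yes | not stated as a reason |

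The fact that unblinds the therapist is known to every patient about their own care. The reason given for one therefore applies to the other.

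**2. Who rates the endpoint**

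The TFI is scored by the patient. Blinding the person who collects the form, or the analyst who processes it, does not mask the person who chooses the scores.

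**3. The plan's own sample size**

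Inputs from Sample size and power: margin 6.5, SD 20, one-sided α 0.025, power 80%, 10% drop-out.

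- Normal approximation: n = 2 × (1.960 + 0.842)² × 20² / 6.5² ≈ 148.6, so 149 per arm.
- Noncentral t: 149 per arm gives power 0.7985 and 150 gives 0.8011, so 150 per arm.
- Drop-out: 150 / 0.90 = 166.7, so 167 per arm and 334 in total.

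The stated figures reproduce. The blinding point does not change them.

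**4. How sensitive the conclusion is to reporting bias (illustration)**

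SE = 20 × √(2/150) = 2.31. Non-inferiority is declared when the observed disadvantage of the blended programme is below 6.5 − 1.96 × 2.31 ≈ 2.0 points.

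Let b be a constant shift in the between-arm difference caused by reporting. The values of b are assumptions; none stands in the document.

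- Bias towards the app, true disadvantage 6.5: P(declare non-inferiority) = Φ(b/2.31 − 1.96).
- Bias towards control, true difference 0: power = Φ((6.5 − b)/2.31 − 1.96).

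| b (TFI points) | False non-inferiority, bias towards app | Power, bias towards control |
|---|---|---|
| 0 | 2.5% | 80.4% |
| 1 | 6.3% | 66.3% |
| 2 | 13.7% | 49.5% |
| 3 | 25.4% | 32.8% |

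**The case against.** Patient blinding is hardly attainable in a trial of this kind, and the Discussion itself says that blinding is typically difficult in physiotherapy studies. Some masking is also real. Baseline is measured before randomisation, and patients may not know what the other arm receives or which arm is the new one. The assessor and analysts are blinded. No sample size, margin or analysis changes. All of this stands. It shows that information about the comparator is limited, but not that patients are blinded to the treatment they receive.

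Several stronger readings are tempting and are not supported:

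- **That all protection against bias is absent.** Assessor blinding still helps outcomes that the assessor measures, and analyst blinding is unaffected.
- **That the withheld detail is allocation concealment.** That term means hiding the next assignment from those who enrol patients. What is described here is limited disclosure to the patient.
- **That control patients can deduce an app arm** because "all included patients should own a smartphone". Nothing in the article shows that they learn of an app, and the consent material is not available.
- **That the therapist administers the iPCQ.** The article says that "patients of the intervention group will be asked to complete this questionnaire at treatment session two, four and six", with sessions four, eight and twelve for control. This fixes the timing and does not say who hands out or sees the form. A contradiction with the blinded-assessor statement is therefore not shown.
- **That the bias favours the app.** Novelty could act that way, but control patients have twice the therapist contact (12 sessions against 6), which could act the other way.

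**Conclusion.** The point holds. The article states twice that patients are blinded, and the design it describes cannot deliver this after allocation. The blinded assessor and analysts do not close the gap for the TFI or the other patient-reported questionnaires. This is an affirmative statement that needs correcting, and the article format does not account for it.

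The effect on the result is undetermined in both direction and size. The figures of about 14–25% false non-inferiority (from 2.5%), or power of about 50–33% (from about 80%), rest on an assumed constant bias of 2 to 3 points, SD 20, 150 analysed per arm and a normal approximation. They show that the conclusion is sensitive to small shifts and are not an estimate of expected harm. The correction should be made because it changes what the trial may claim about protection from bias on its primary endpoint.

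**What to change.** 1. In Study design and randomisation procedure and in the Discussion, replace the patient-blinding statements with wording such as: assessor- and analyst-blinded; patients given limited information before randomisation, but patients and therapist not blinded to treatment received.
2. Treat the TFI and the other questionnaires as unblinded patient-reported outcomes when drawing the non-inferiority conclusion, and state the risk of bias in either direction.
3. Have every questionnaire, including the iPCQ at treatment sessions, completed directly by the patient without the therapist. Data Availability already names RedCap, which supports online surveys.
4. Name assessor-measured neck and jaw mobility as supportive. Loudness matching is unsuitable for this role, because its forced-choice procedure depends on the patient's responses.
5. If expectancy is asked after allocation, report it descriptively only. Do not adjust the TFI effect for it: treatment can affect the answer, so adjustment would lose the protection of randomisation and could remove part of the effect.

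The cost is rewording, a small change in how forms are completed, and a less favourable blinding label. Sample size, margin and primary analysis stay as they are.
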